## Abstract

**Background:**

Intensive care unit (ICU)-acquired weakness (ICU-AW) is one of the most common complications of post-ICU syndrome. It is the leading cause of gait disturbance, decreased activities of daily living, and poor health-related quality of life. The early rehabilitation of critically ill patients can reduce the ICU-AW. We designed a protocol to investigate the feasibility and safety of conventional rehabilitation with additional in-bed cycling/stepping in critically ill patients.

**Methods:**

The study is designed as a single-center, single-blind, pilot, randomized, parallel-group study. After the screening, participants are randomly allocated to two groups, stratified by mechanical ventilation status. The intervention group will be provided with exercises of in-bed cycling/stepping according to the level of consciousness, motor power, and function in addition to conventional rehabilitation. In contrast, the control group will be provided with only conventional rehabilitation. The length of intervention is from ICU admission to discharge, and interventions will be conducted for 20 minutes, a maximum of three sessions per day.

**Results:**

The outcomes are the number and percentage of completed in-bed cycling/stepping sessions, the duration and percentage of in-bed cycling/stepping sessions, and the number of cessations of in-bed cycling/stepping sessions, the interval from ICU admission to the first session of in-bed cycling/stepping, the number and percentage of completed conventional rehabilitation sessions, the duration and percentage of conventional rehabilitation sessions, the number of cessations of conventional rehabilitation sessions, the number of adverse events, level of consciousness, functional mobility, muscle strength, activities of daily living, and quality of life.

**Discussion:**

This study is a pilot clinical trial to investigate the feasibility and safety of conventional rehabilitation with additional in-bed cycling/stepping in critically ill patients. If the expected results are achieved in this study, the methods of ICU rehabilitation will be enriched.

**Trial registration:**

clinicialtrials.gov, Clinical Trials Registration #NCT05868070.

## Introduction

The prevention of post-intensive care syndrome has been gaining great interest with the improvement in survival rates of critically ill patients [1]. Post-intensive care syndrome indicates physical, cognitive, and mental complications, including critical illness neuropathy and myopathy, disuse atrophy, memory, and executive dysfunction, depression, post-traumatic stress disorder, and anxiety [2]. Intensive care unit (ICU)-acquired weakness (ICU-AW) is one of the most common complications of post-ICU syndrome [3]. It is the main cause of gait disturbance, decreased activities of daily living (ADL), and poor health-related quality of life, which may occur and even persist after ICU discharge [4].

Early rehabilitation is crucial to mitigate ICU-AW [5]. The incidence and severity of ICU-AW, along with the duration of mechanical ventilation, ICU length of stay, functional independence, and mortality, can be improved as a result of early rehabilitation [6, 7]. However, effective rehabilitation is frequently hampered in the ICU setting due to disease status, disorganized behavior, sedation, insertion of tubes and catheters in critically ill patients, and insufficient rehabilitation resources [8]. Thus, developing rehabilitation protocols and settings as a patient-tailored approach is necessary for early rehabilitation with proper dose and intensity.

As an adjunctive method to accomplish effective ICU rehabilitation, the utilization of in-bed exercise equipment has been attempted in critically ill patients. An in-bed cycle ergometer is one of the options that can be applied in the ICU [9]. It has been generally recognized to prevent contracture, increase blood circulation, improve cardiopulmonary function, and strengthen the lower limb muscles with fewer safety issues [10, 11]. Additionally, it is likely that stepping has additive effects on cycling [12], regarding the opportunity for gait imitation to perform reciprocal limb movements and mechanical stress on bones and muscles to bear body weight [13]. If both the cycle ergometer and stepper are applied together to critically ill patients, their effect on functional mobility or strength would be more enhanced than if only in-bed cycle ergometers were used.

Caution should be taken to provide early rehabilitation in the ICU setting because critically ill patients can be vulnerable to hemodynamic and respiratory changes, and endotracheal or nasogastric tubes and vascular or urinary catheters can be accidentally removed despite their low incidence [14]. The establishment of safety criteria considering vital signs, level of consciousness and cooperation, sedation state, administration of vasopressors, types of catheters or tubes in situ, and wounds can be made mandatory to determine whether to delay or terminate rehabilitation sessions [15, 16]. The safety criteria for the application of the in-bed cycle ergometer and stepper may need to be modified in consideration of the increased and frequent range of motion at the lower extremities compared to early active mobilization during exercises.

While previous clinical trials have incorporated in-bed cycling as ICU rehabilitation in critically ill patients [17, 18], few studies have been published that simultaneously employ both in-bed cycling and stepping exercises. Therefore, we designed a pilot randomized controlled clinical trial protocol to investigate the feasibility and safety of conventional rehabilitation with additional in-bed cycling/stepping in critically ill patients.

## Methods

### Trial design and study setting

This is a prospective, single-blind, assessor-blinded, add-on, single-center, two-arm parallel, pilot, randomized controlled trial. This protocol adhered to the Standard Protocol Items: Recommendations for Interventional Trials (SPIRIT) guidelines [19] (see S1 Table) and TIDier checklist [20] (see S2 Table). Inclusion criteria are critically ill patients who are aged 45 years or older, are admitted to ICU less than 72 hours before randomization, are deemed to need ICU care for more than 48 hours, and have Functional Ambulation Category (FAC) 2 or higher before admission to the ICU. Exclusion criteria are as follows: any neurological disorders, including acute stroke, advanced dementia, hypoxic-ischemic encephalopathy, amyotrophic lateral sclerosis, myasthenia gravis, and/or acute inflammatory demyelinating polyradiculoneuropathy; the presence of acute deep venous thrombosis and/or pulmonary embolism; pneumothorax; an external fixator, superficial metallic implants, amputations, and/or eschar in the lower extremities; expected ICU discharge within 3 days of admission; pregnancy; difficulty in obtaining informed consent; the life expectancy of less than six months. The inclusion and exclusion criteria are presented in Table 1. A member of the study team will obtain written consent during ICU admission for a baseline evaluation, and the research process will not proceed until consent is obtained. Through screening, the members of the research team will verify their eligibility.

**Table 1 pone.0301368.t001:** Inclusion and exclusion criteria.

Inclusion criteria	Exclusion criteria
• Age ≥ 45 •Admission of ICU ≤ 72 hours •Patient deemed to need ≥ 48 hours of ICU care •Premorbid Functional Ambulation Category ≥ 2	ㆍNeurological disorders ㆍ Central nervous system: acute stroke, advanced dementia, hypoxic-ischemic encephalopathy ㆍ Peripheral nervous system: amyotrophic lateral sclerosis, myasthenia gravis, acute inflammatory demyelinating polyradiculoneuropathy ㆍAcute deep venous thrombosis, pulmonary embolism ㆍPneumothorax ㆍExternal fixator, superficial metallic implants, amputation, eschar, etc. ㆍExpected ICU discharge within 3 days of admission ㆍPregnancy ㆍDifficulty in obtaining informed consent (rejection, no family, if the family does not agree) ㆍIf the life expectancy is less than 6 months

### Recruitment

Clinicians in the ICU at our hospital will collaborate to enroll patients for this clinical trial. Additionally, posters about this study are planned to be affixed on the noticeboard in front of the ICU, facilitating easy access to information regarding the clinical trial for representatives of patients. The principal investigator will provide a detailed explanation of the study to the participants’ legal representatives since most admitted patients are critically or severely ill. The study will not exclude patients who are likely to participate based on their socioeconomic status. This study is a pilot clinical trial to investigate the feasibility and safety of in-bed cycling/stepping exercise intervention and aims to recruit at least 24 participants. Assuming a 20% loss for death and a 15% loss for follow-up, the required sample size was 12 per arm to be recruited in this study.

### Allocation

The computer-generated sequence will be generated on the website (https://mrcc.snuh.org) by an independent institution in our hospital. A computer-generated sequence will randomly allocate the two groups in this study. The stratified block randomization method will assign the randomization table to the control or intervention group at a 1:1 ratio. The use of mechanical ventilation will stratify the participants.

The group allocation will be performed by an independent researcher who is not involved in evaluating outcomes and will be concealed to physiotherapists who are engaged in assessing outcomes. The participants and in-bed cycling/stepping intervention provider will be instructed not to disclose the allocation to the evaluator. After the end of the clinical trial, blinding will be maintained until the input of evaluation data is completed. Any unblinding prior to clinical trials due to accidental or serious adverse events should be documented. To promote data quality for assessment and collection of outcomes, assessors will be well-trained.

### Interventions

#### Conventional rehabilitation

Patients in the control group will only receive conventional rehabilitation in the ICU. The protocol for conventional rehabilitation in the ICU is shown in Fig 1. An standardized stepwise ICU rehabilitation program is provided for 20 min based on the stage of the patient’s condition, which is evaluated prior to each treatment session and considers consciousness, motor power, and functional mobility according to previous studies [10, 15]. The stage of the patient’s condition is graded as the 7-Likert scale from red (least able) to violet (most able) [21, 22], which means that the patient’s state of consciousness, muscle strength, and function improve sequentially. Generally, rehabilitation for critically ill patients is performed depending on the condition of critically ill patients [23, 24]. The goal of the conventional rehabilitation at each stage is lying without contractures, turning self, sitting balance, sitting at the edge, standing and transferring from bed to chair, assisted gait, and gait endurance. The conventional rehabilitation is provided by physiotherapists from ICU admission to hospital discharge, and the routine frequency of conventional rehabilitation is one session per day during weekdays.

**Fig 1 pone.0301368.g001:**
[figure not shown]
ICU rehabilitation protocol with exercise intervention using in-bed cycle ergometer/stepper. Critically ill patients will be classified from red to violet according to Richmond agitation-sedation scale (RASS), motor power, and level of consciousness. The patients in the control group will receive conventional rehabilitation according to the ICU rainbow mobilization scale program including range of motion (ROM), sitting, standing, and ambulation. Critically ill patients in the intervention group will receive in-bed cycling/stepping intervention starting from Yellow to Violet in addition to the conventional rehabilitation. As the condition of the critically ill patient improves from Yellow to Violet, the exercise intervention gradually progresses to passive, active assistive, active, and resistive exercise modes. In-bed cycling/stepping is provided by physiotherapists from ICU admission to discharge, and the routine frequency of in-bed cycling/stepping is 1–3 sessions per day on the weekdays during ICU hospitalization. The number of in-bed cycling/stepping will be increased gradually. Cycling is performed if there is one session per day; cycling-stepping is performed if there are two sessions per day; and cycling-stepping-cycling is performed if there are three sessions per day. ROM: range of motion; UE: upper extremity; LE: lower extremity.

#### In-bed cycling/stepping

Patients in the intervention group will receive conventional rehabilitation plus exercise intervention with an in-bed cycle ergometer/stepper for additional 20 min in the ICU. The protocol, including exercise intervention, was developed by modifying the rainbow mobilization scales and the existing intensive care rehabilitation protocol shown in Fig 1. As the condition of the critically ill patient improves from yellow to violet, the intervention gradually progresses to passive, active assistive, active, and resistive exercise. In-bed cycling/stepping is provided by physiotherapists from ICU admission to discharge, and the routine frequency of in-bed cycling/stepping is 1–3 sessions per day on the weekdays during ICU hospitalization. The number of in-bed cycling/stepping interventions will gradually be increased depending on the patient’s condition [23]. Cycling is performed if there is one session per day; cycling-stepping if there are two sessions per day; and cycling-stepping-cycling if there are three sessions per day. During the intervention, the target rating of perceived exertion ranges from moderate to hard, and the exercise intensity is adjusted in this range [25, 26].

Risk criteria for delaying or terminating ICU rehabilitation will be assessed to determine patients’ suitability to participate in rehabilitation before and during rehabilitation sessions (Table 2) [15, 16]. ICU rehabilitation should be delayed or ceased if there is no recovery within two minutes under any of the conditions. Adverse events will be recorded after rehabilitation sessions. To improve intervention adherence, the participants are provided with an exercise log. Usual care, such as pulmonary rehabilitation and occupational therapy, will be maintained for all patients during the trial. Additionally, usual care will be maintained for all patients following trial completion.

**Table 2 pone.0301368.t002:** Criteria for delaying or terminating ICU rehabilitation and exercise intervention.

Respiratory conditions
ㆍPercutaneous oxygen saturation (SpO_2_) < 88% ㆍRespiratory rate (RR) > 40bpm ㆍUnsecure airway

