**Outcomes**
ㆍThe number and percentage of completed in-bed cycling/stepping sessions ㆍThe duration and percentage of in-bed cycling/stepping sessions ㆍThe number of cessations of in-bed cycling/stepping sessions
ㆍThe interval from ICU admission to the first session of in-bed cycling/stepping ㆍ The number and percentage of completed conventional rehabilitation sessions ㆍ The duration and percentage of conventional rehabilitation sessions ㆍ The number of cessations of conventional rehabilitation sessions ㆍ The number of adverse events ㆍ Level of consciousness: Richmond agitation-sedation scale (RASS), confusion assessment method for the ICU (CAM-ICU) ㆍ Mobility: functional ambulatory category (FAC), functional status score (FSS-ICU), short physical performance battery score (SPPB), de Morton Mobility Index (DEMMI), falls efficacy scale (FES), activities-specific balance confidence scale (ABC) ㆍMotor power: sum of Medical Research Council (MRC) score, hand grip strength (HGS) ㆍActivities of daily living (ADL): modified Barthel index (MBI) ㆍQuality of life (QOL): 36-item short form survey (SF-36) version 2.0 ㆍOthers: Pittsburgh rehabilitation participation scale (PRPS), days to initiate ambulation (FAC ≥2), mortality-28 days, duration of mechanical ventilation, length of stay in the ICU, length of stay in the hospital, concomitant occupational therapy and its application dose, concomitant pulmonary rehabilitation and its application dose

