### Adverse events

In this clinical trial, adverse events are all undesirable medical events that cause symptoms that were not observed before the start of the clinical trial, listed in Table 4. Predicted adverse events include falls, fractures, severe pain, endotracheal tube removal, arterial line removal, central line removal, arrhythmia, bradycardia, systolic blood pressure > 200 mmHg, systolic blood pressure < 90 mmHg due to hemodynamic instability during exercise, desaturation ≤ 88% due to respiratory instability during exercise and other minor adverse reactions, such as dyspnea, dizziness, tachypnea, and sinus tachycardia [7, 28, 29]. Predicted side effects are also classified as adverse events, and the severity of adverse reactions is classified into mild, moderate, and severe. The frequency of adverse events that are both relevant and irrelevant to the investigational device will be recorded. In the case of unexpected serious adverse events or other unintended trial interventions over the course of the study, we will report to the institutional review board. Data and safety monitoring will be conducted for every five-participant registration.

**Table 4 pone.0301368.t004:** Lists of predicted adverse events.

Adverse events
Fall •Fracture •Severe pain •Endotracheal tube removal •Arterial line removal •Central line removal •Arrhythmia •Bradycardia •Systolic blood pressure > 200 mmHg or < 90 mmHg due to hemodynamic instability during exercise •Desaturation ≤ 88% due to respiratory instability during exercise •Other minor adverse reactions such as dyspnea, dizziness, tachypnea, and sinus tachycardia

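### Adverse event recording is tied to rehabilitation sessions, which are more frequent in the intervention arm, and the outcome is a count without a denominator, so background events may be detected unequally

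*Protocol article*

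**What the plan says.** The section In-bed cycling/stepping of the protocol article fixes when events are noted: "Adverse events will be recorded after rehabilitation sessions". No other recording occasion is stated for either arm.

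The arms differ in the number of sessions. Under Conventional rehabilitation, which both arms receive, "the routine frequency of conventional rehabilitation is one session per day during weekdays". The add-on comes on top of this: "Patients in the intervention group will receive conventional rehabilitation plus exercise intervention with an in-bed cycle ergometer/stepper for additional 20 min in the ICU", and "the routine frequency of in-bed cycling/stepping is 1–3 sessions per day on the weekdays during ICU hospitalization". The caption of Fig 1 limits when the add-on begins: intervention patients "will receive in-bed cycling/stepping intervention starting from Yellow to Violet in addition to the conventional rehabilitation".

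The Adverse events section is broader than sessions. It says that "adverse events are all undesirable medical events that cause symptoms that were not observed before the start of the clinical trial", and that "The frequency of adverse events that are both relevant and irrelevant to the investigational device will be recorded". Table 4 lists some events without reference to exercise (arrhythmia, bradycardia, line or tube removal). It ties others, the blood pressure and desaturation events, to exercise.

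The outcome in Table 3 is "The number of adverse events", with no denominator, whereas session completion in the same table is given as number and percentage. Statistical methods contains only a general rule: Mann-Whitney U for continuous outcomes, and chi-square or Fisher's exact test for the others, between the two groups.

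**The concern.** Safety is one of the trial's two stated aims. Critically ill patients have arrhythmias, bradycardia and similar events whether or not they exercise. If such an event is written down when a therapist completes a session record, the arm with more sessions gets more chances to record it. The intervention arm could then show more events even if its patients had no more of them.

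A count without a denominator cannot resolve this. An excess could be real harm from the extra sessions or an effect of looking more often. Reviews of accumulating safety data, planned for every five participants registered, would meet the same ambiguity if they draw on the same records. An analysis plan can add denominators later, but it cannot supply control-arm events that were never recorded.

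**Working it through.** **Plan's own figure.** The protocol gives no figure for the adverse event comparison. The only design figure used here is 12 per arm (Recruitment).

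**Step 1: recording occasions per ICU weekday.** Control: 1 conventional session. Intervention from stage Yellow: 1 conventional + 1 to 3 device sessions = 2 to 4. The ratio r is 2, 3 or 4. Below Yellow, and on the ward after the ICU, both arms have one session and the ratio is 1.

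**Step 2: average ratio over the ICU stay.** Let s be the share of ICU weekdays below Yellow. The documents do not give s, so a range is shown. Average ratio = s + (1 − s) × r.

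| s (assumed) | r = 2 | r = 3 | r = 4 |
|---|---|---|---|
| 0 | 2 | 3 | 4 |
| 0.25 | 1.75 | 2.5 | 3.25 |
| 0.50 | 1.5 | 2.0 | 2.5 |
| 0.75 | 1.25 | 1.5 | 1.75 |

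**Step 3: effect on patients with at least one recorded event.** Assume that background events are recorded only through sessions, with the same expected number m per session in both arms, over 5 ICU weekdays. Neither m nor the number of weekdays is in the documents. With Poisson counts, P(at least one) = 1 − exp(−5 × m × ratio).

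| m | Control (ratio 1) | Ratio 1.5 to 2.5 | Ratio 2 to 4 |
|---|---|---|---|
| 0.02 | 9.5% | 13.9% to 22.1% | 18.1% to 33.0% |
| 0.05 | 22.1% | 31.3% to 46.5% | 39.3% to 63.2% |
| 0.10 | 39.3% | 52.8% to 71.3% | 63.2% to 86.5% |

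For example, at m = 0.05 and ratio 2.5: 1 − exp(−0.625) = 46.5%.

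**Step 4: effect on the general test rule.** Under the same assumptions, with 12 per arm and 2,000 simulated trials per setting, a two-sided 5% Mann-Whitney test on counts per patient rejected as follows:

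| m | Ratio 1 | Ratio 2 | Ratio 3 | Ratio 4 |
|---|---|---|---|---|
| 0.02 | 1% | 5.5% | 14% | 26% |
| 0.05 | 4% | 14% | 35% | 58% |
| 0.10 | 4% | 25% | 60% | 90% |

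For background events, every rejection above the ratio-1 column comes from detection. For events that sessions cause, the same rejection would be correct, because intervention patients would really have more of them. The count alone cannot tell the two apart.

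**Step 5: what an absence of events would show.** With no event in 12 patients, the exact one-sided 95% upper bound is 1 − 0.05^(1/12) = 22.1%.

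**Limit of steps 3 and 4.** They describe the extreme in which nothing is captured outside sessions and each session adds new recorded events. If a session record also covers the hours since the previous one, or if staff note events from the chart, the detection ratio is closer to 1.

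**The case against.** The strongest objection concerns a reading that a reader might infer: that more sessions in one arm confound the safety comparison by exposure. The documents do not support it. This is a randomized add-on trial and the extra sessions are the intervention. Events they cause belong to its effect, and comparing events per randomized patient estimates the total harm of the programme. A per-session rate answers a different question and should not replace that comparison. This stands in full; what remains is unequal detection.

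Second, capture outside sessions is not ruled out. The Adverse events section defines events broadly, counts device-unrelated ones and requires unexpected serious events to be reported to the review board. The recording sentence does not say that events are recorded only after sessions. This stands in part: unequal detection is a risk created by the stated rule, not an established fact. But the broad definition comes with no schedule that would put it into practice equally in both arms.

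Third, the ratio of two to four holds only from Yellow and only in the ICU, and device sessions are increased gradually. This stands and is allowed for in step 2.

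Fourth, denominators and rate models are commonly left to an analysis plan, and session counts and ICU stay are already collected. This answers the reporting half, not the collection half.

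**Conclusion.** The point holds as one of unequal detection. The only stated recording occasion is the rehabilitation session, and intervention patients have more of these: two to four against one per ICU weekday from stage Yellow, and 1.5 to 2.5 on average if half of ICU weekdays are below Yellow. Background events are therefore more likely to be recorded in the intervention arm, and a bare count cannot separate this from harm caused by the added sessions. The percentages in steps 3 and 4 rest on assumed event rates, five ICU weekdays and capture through sessions alone; they show how large the effect could be and are not predictions.

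Two further readings are tempting but are not in the protocol. It does not plan a chi-square test on event totals: no test specific to adverse events is named, and a count per patient under Mann-Whitney uses one value per patient. Nor does it say that a non-significant difference will be taken as evidence of safety. The per-patient comparison by arm remains valid once detection is equal.

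**What to change.** **Collection.** State one adverse event schedule that applies to both arms and does not depend on sessions, for example a daily chart check through the ICU stay. Keep the record made after each session, and flag in-session events separately.

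**Reporting.**
- (a) Events per patient and per ICU patient-day, by arm.
- (b) In-session events per session delivered, separately for conventional, cycling and stepping sessions.
- (c) Patients with at least one event, by arm, with exact confidence intervals, including the upper bound when none is seen (22%, one-sided 95%, for 0 of 12).

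**Cost.** A short daily chart check by existing staff, and a few sentences of text. Session counts and length of ICU stay are already outcomes in Table 3, so the denominators need little or no new data. The collection change should be made before or early in recruitment, because missed control-arm events may be hard to recover. The reporting items can go into the analysis plan.
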